## Methods and analysis

The study is a quasiexperimental design,^1^ comparing changes in measurement and assessment for alcohol consumption and comorbid depression, and, if needed, advice and/or referral for treatment between PHCUs in intervention municipal areas and PHCUs in similar control municipal areas. In 2017, prior to a grant application, we published a preprotocol for a three-country study to test the scale-up of PHC-based programmes to identify and manage the harmful use of alcohol and comorbid depression.^60^ Since the application, and during the grant negotiation and planning phase, the design of the study has changed considerably, essentially moving from a two-arm design to a four-arm design, and changing the primary outcome measure to the proportion of the adult population registered with a PHCU that has their alcohol consumption measured, online supplementary file S1, online supplementary box S1. With all changes approved by the concerned ethics committee, this paper outlines the final protocol for a quasiexperimental study to test the implementation of PHC-based measurement, advice and treatment for heavy drinking and comorbid depression at the community level in three Latin American countries, Colombia, Mexico and Peru (SCALA study).

10.1136/bmjopen-2020-038226.supp1Supplementary data

10.1136/bmjopen-2020-038226.supp2Supplementary data

Intervention municipal areas are investigator-selected from Bogotá (Colombia), Mexico City (Mexico) and Callao—Lima (Peru). Control municipal areas are investigator-selected in the same cities, on the basis of comparability with the intervention municipal area in terms of socioeconomic and other characteristics which impact on drinking, healthcare and survival, comparable community mental health services and sufficient geographical separation to minimise spill over effects from the intervention municipal area. Randomised selection of the municipal areas was not feasible due to organisational limitations. Municipal areas are chosen as a scalable implementation unit at mesosystem level that can be replicated as the intervention is scaled-up,^40^ given their jurisdictional responsibilities for prevention and healthcare services.

Within each intervention municipal area, a local Community Advisory Board (CAB) is created of key stakeholders, including representatives of local and regional government, directors of PHC services, non-governmental organisations active in providing counselling and treatment services for alcohol and mental health, academic experts and local media. The CABs meet regularly during the course of the study, giving advice on tailoring materials for local use, giving advice on adoption mechanisms, support systems and communication campaigns to support the action and preparing for sustainability and scale-up at the end of the action.

The units of allocation and analysis, that is, study participants, are 54 PHCUs and the providers working in them. Within each PHCU, eligible providers include any fully trained healthcare provider working in the PHCU and involved in medical and/or preventive care. Within each PHCU, individual providers decide themselves whether or not to participate in the study; those who do sign an informed consent for their participation. Based on the five-country ODHIN study, we estimate that approximately two-fifths of providers will consent to join the study.^61^ The overall study design is summarised in figure 1. Fifty-four PHCU are invited to join the study until 27 are achieved within each of the two municipal areas (intervention and control) across the three countries (nine per municipal area within each of the three countries).

**Figure 1 F1:**
[figure not shown]
Study flow diagram.

Within each intervention municipal area, a user panel (UP) is created of providers and patients drawn from the PHC centres to advise on the tailoring of patient and provider materials and on provider training programmes.

For the first 6 months of the 18-month implementation and test period, a four-arm design is adopted, figure 2. Within the comparator municipal area, 12 PHCUs out of the 27 are randomly allocated to control (Arm 1), and 15 are allocated to receive short training to implement a short clinical package (Arm 2). Within the intervention municipal area, in which all 27 PHCU receive municipal action, 15 PHCUs are randomly allocated to receive short training to implement a short clinical package (Arm 3), and 12 PHCUs are allocated to receive standard training to implement a standard clinical package (Arm 4). Random allocation was undertaken using Excel random number generator.

**Figure 2 F2:**
[figure not shown]
Study design for the first 6 months of the 18-month implementation period.PHCU, primary healthcare units.

The clinical package comprises measurement instruments, patient information and advice material and provider guidance material, with the differences between the standard and short clinical materials are described in online supplementary file S1, online supplementary table S1, with references. Online supplementary file S1, online supplementary table S1 also lists the material used in control Arm 1. The standard material is essentially that used in common clinical practice^60^ and the short version a simplified version deliverable in practice during a short period of time. The packages include measurement instruments and patient advice material for comorbid depression implemented with patients with an AUDIT-C score of 8+. Online supplementary file S1, online supplementary table S1 summarises the differences between the standard and short versions of the training programme.

The standard and short care pathways that are implemented are summarised in online supplementary file S1, online supplementary figures S1 and S2.

Essentially, in all arms, PHC providers are asked to measure the alcohol consumption of all adult patients who consult for whatever reason using AUDIT-C. The three AUDIT-C questions are included in a paper tally sheet completed by the provider, in which the providers document the outcome of the consultation (advice given, patient referred, etc). The local researchers visit each PHCU on a 2–4 weekly basis to collect completed tally sheets and deliver new tally sheets as required. The local researchers collect information on the total number of adult patients (aged 18+ years) registered with each PHCU and the monthly number of total adult consultations with each provider. Patients who score <8 with AUDIT-C are given a patient information leaflet. Patients who score 8+ with AUDIT-C are assessed and manged as appropriate for depression, and are advised to reduce their alcohol consumption, unless there are clinical indications for referral. Arm 4 differs from Arm 3 in having a lengthier assessment, if indicated, and a longer session of advice giving.

By Month 6, Hypothesis 3, that is, non-superiority of Arm 4 (standard package with municipal action and standard training) over Arm 3 (short package with municipal action and short training) will be tested. In the presence of clinical equivalence of a relative difference of the primary outcome, that is, the cumulative coverage of patients whose alcohol consumption is measured, of less than 10%, Arm 4 will be replaced by Arm 3 from month 8 onwards, figure 3.

**Figure 3 F3:**
[figure not shown]
Study design from month 8 onwards, assuming no superiority of Arm 4 over Arm 3 during first 6 months of implementation. PHCU, primary healthcare units.

The municipal integration and support inputs to Arms 3 and 4 within the intervention municipal area are summarised in online supplementary file S1, online supplementary table S2, with references. Municipal integration and support comprises:

Creation of local CAB of local stakeholders to advise on tailoring of materials, support local implementation and review drivers of successful action.Appointment of local project champion to advocate for successful implementation of programmes.Implementation of five evidence-based adoption mechanisms.Implementation of five evidence-based support systems.Implementation of community-based communication campaigns.

### Tailoring

The CABs and UPs review and tailor relevant materials of the clinical package and training courses and of the municipal integration and support inputs within the seven domains of: (1) local and national guideline factors; (2) individual healthcare provider factors; (3) patient factors; (4) interactions between different professional groups; (5) incentives and resources; (6) capacity for organisational change and (7) social, political and legal factors.^62–64^

The study timetable is summarised in figure 4. The data management plan, as submitted to the European Commission, is available as online supplementary file S2.

**Figure 4 F4:**
[figure not shown]
Study timetable.

### Data collection and instruments

#### During set-up phase for Arms 1–4

##### *​*Municipal level information

At the level of the municipal area (or, when not available, at whole city, regional or country level), the following information will be collected from routinely available data on sociodemographic factors, alcohol and mental health data, health system structures, quality of life, sustainable governance and values, online supplementary file S1, online supplementary table S3.

##### PHCU and provider level information

All contacted PHCU, including those who did and did not agree to be part of the study, will provide information on the following:

Numbers of registered patients, divided into age 0 to 17 years and 18+ years.Numbers and professions of provider staff (including physicians, nurses, nurse technicians, midwifes, psychologists, social workers and others).

At recruitment, PHC providers will provide data on their:

Age.Gender.Profession (doctor, nurse, practice assistant, etc).Time worked in the PHC.Data on their attitudes and experiences to working with patients with heavy drinking and comorbid depression (online supplementary file S1, online supplementary table S4).

Since we are unable to randomise the municipal areas involved, we will use propensity score matching (PSM) based on data collected at the level of the municipal area and the PHCU, to take into account potential confounding variables between control and intervention municipal areas, and minimise bias on account of these.

#### During 1-month baseline measurement period for Arms 1–4

##### Provider-based measurement and assessment of alcohol consumption and comorbid depression and record of advice and treatment given (tally sheets)

Based on the validated methodology of the ODHIN project,^22 24^ PHC providers will be asked to document activity by completing anonymous paper tally sheets that record eligible patients’ (aged 18+ years) AUDIT-C scores,^65^ and, if administered (as documented in online supplementary file S1, online supplementary table S1), AUDIT-10,^66^ Patient Health Questionnaire (mental disorders), 2-item version (PHQ-2)^67^ and PHQ-9^68^ scores, and the advice or treatment given to each patient. The tally sheets will record the age, sex and educational level of the patient, the latter as a proxy measure of socioeconomic status. PHCUs will return data on the number of adult (aged 18+ years) consultations per provider for the 1-month baseline measurement period. Tally sheets will be delivered to the PHCU to be distributed to the participating providers at the beginning of the 1-month baseline measurement period and collected at the end of the period, with no other contact during the period.

#### During training prior to implementation for Arms 2–4

Providers will complete a short questionnaire after the initial training sessions. The questionnaires, which are adapted based on specific training contents (standard or short package), will assess the participants’ experience of the training, measuring satisfaction with the components of the training aspects, as well as their perceived utility. Two measures included in the main provider questionnaires, Short Alcohol and Alcohol Problems Perception questionnaire (SAAPPQ)^69^ and self-efficacy,^70^ will be included in order to assess the specific impact of the training, independent of the effect of the implementation of the intervention.

#### During 18-month implementation period for Arms 1–4

##### Provider-based measurement and assessment of alcohol consumption and comorbid depression and record of advice and treatment given (tally sheets)

The same mechanism, for tally sheets used during the baseline measurement period will continue for each calendar month of the 18-month implementation period. Tally sheets will be delivered monthly to each PHCU to distribute to participating providers. Completed tally sheets will be collected at the end of each month. Following training in Arms 2–4, and municipal support in Arms 3–4, each provider determines use and completion of the tally sheets, with no additional prompting. Monthly data will be collected and reported with accumulation of coverage over time. Formal reporting will be undertaken at baseline, and for coverage achieved by month 12 and by month 18 of the 18 month implementation and test period. Tally sheets will include an identifying code of the provider, PHCU, country and study arm, but no identifying code of the patient. Data will be extracted and sent to the project’s data warehouse at Technical University Dresden on a monthly basis.

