### Outcomes

#### Primary outcome

The primary outcome will be the cumulative proportion of the number of adults (aged 18+ years) registered with the PHCU that have their alcohol consumption measured with a completed AUDIT-C instrument during the study period (coverage). The number of adults registered is provided by the administrative office of the PHCU and includes all adult patients covered by the PHCU, whether or not they consult during the 18-month implementation test period.

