### Statistical tests of key hypotheses

#### Primary study goal

Multilevel regression analyses will be undertaken at 12 months’ time of the implementation test period, using cumulative results at months 1 to 12, and at 18 months’ time using cumulative results months 1 to 18. Both analyses will include covariates of country and results during baseline month, analysed at the levels of the PHCU by study arm, taking into consideration the hierarchical nature of the data. For any PHCU that drops out during the study, outcome values for subsequent measurement points will be set at the last value obtained.

##### Hypothesis 1

Municipal action leads to more sustainable coverage among PHCU that receive training. We will compare results on primary outcome after 18 months with results after 12 months between Arm 3 versus Arm 2 via regression.

Dependent variables:

For each PHCU, cumulative results of months 1–18 of number of patients whose alcohol consumption is measured with AUDIT-C per 1000 registered patients; and cumulative results of months 1–12 per 1000 registered patients.

Random effects:

Country as random intercept (test for inclusion).

Independent variables:

Proportion of consulting patients who have their alcohol consumption measured with a completed AUDIT-C instrument during the baseline measurement month.Condition:Municipal action (yes vs no).Covariate:Proportion of consulting patients who have their alcohol consumption measured with a completed AUDIT-C instrument during the baseline measurement month.

It is postulated that coverage for Arm 3 will be significantly higher than for Arm 2.

##### Hypothesis 2

Training leads to higher coverage than no training. For both months 1–12 and months 1–18, compare cumulative coverage as per primary outcome between Arms 1 and 2 via multilevel regression analyses.

Dependent variable

Cumulative results months 1–12, and cumulative results months 1–18 of number of patients whose alcohol consumption is measured with AUDIT-C per 1000 registered patients withPHCU.

Random effects:

Country as random intercept (test for inclusion).

Independent variables:

Condition:Training (Arm 2 vs Arm 1).Covariate:Proportion of consulting patients who have their alcohol consumption measured with a completed AUDIT-C instrument during the baseline measurement month.

It is postulated that coverage for Arm 2 will be significantly higher than for Arm 1.

##### Hypotheses 3

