### Sample size calculations for main hypothesis

As the outcome of the primary study goal is predicted to be Arm 3>Arm 2>Arm 1, we compared both Arm 2>Arm 1, and Arm 3>Arm 2.

Our power calculations are based on the following assumptions: given an average size of a PHCU of approximately 15 000 adults, with an average of 1500 new consultations per month, we expect a cumulative coverage after 12 months of 0.0325 of the registered adult population to have had their alcohol consumption measured in the control condition (Arm 1) (data extrapolated from month 3 and month 9 assessments of control group from ODHIN study;^22 24^ [name], personal communication). For the short clinical package and short training (Arm 2), we expect this to increase to 0.075 (data extrapolated from month 3 and month 9 assessments of training group from ODHIN study;^22 24^ [name], personal communication). Although the WHO Phase IV study predicts an additional beneficial impact of municipal support,^41^ precise empirical data is not available—however, we consider an estimate for Arm 3, with municipal support, to be 0.15, a proportion that would need to be achieved to consider municipal support to be worthwhile. To detect the difference between Arm 2 and Arm 1, assuming a design effect of 15 PHCUs (clusters) across the three municipal areas in Arm 2, with 15 000 patients (items), and 12 PHCUs (clusters) in Arm 1, with 15 000 patients (items), with an ICC for PHCUs of 0.03 (data from ODHIN study;^22 24^ [name], personal communication) we would have 82% power at a significance level of 5%.^87^ For the difference between Arm 3 and Arm 2 (15 PHCUs/clusters in each arm), we would have 96.5% power.

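### Coverage is defined on distinct registered adults, but the anonymous tally sheets as described cannot tell a repeat AUDIT-C from a first one, so the numerator counts measurements rather than people

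*Protocol article*

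**What the plan says.** **The unit of the outcome is a person.** The Primary outcome section defines coverage as the "cumulative proportion of the number of adults (aged 18+ years) registered with the PHCU that have their alcohol consumption measured". The regressions in the Primary study goal section use the "number of patients whose alcohol consumption is measured with AUDIT-C per 1000 registered patients", cumulated over months 1–12 and 1–18.

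**The unit of the data is a sheet.** The tally-sheet section for the 18-month implementation period states: "Tally sheets will include an identifying code of the provider, PHCU, country and study arm, but no identifying code of the patient". The baseline tally-sheet section lists the patient data recorded: "The tally sheets will record the age, sex and educational level of the patient". On accumulation, the implementation section says: "Monthly data will be collected and reported with accumulation of coverage over time". The extended tally sheets used for quality control carry no patient code either.

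**Who is measured.** In Methods and analysis, after Figure 2, "PHC providers are asked to measure the alcohol consumption of all adult patients who consult for whatever reason using AUDIT-C". The article does not limit this to once per patient. Use of the sheets is left to each provider, without further prompting.

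**Volume.** The sample size section assumes about 15,000 adults per PHCU, "with an average of 1500 new consultations per month", and 12-month coverage of 0.0325, 0.075 and 0.15 in Arms 1, 2 and 3.

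**The concern.** A proportion of adults needs each adult counted once. Age, sex and education cannot reliably link two sheets from the same person among some 15,000 registered adults, so repeats cannot be removed afterwards. This is not a detail that an analysis plan can settle later, because the information is not collected.

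The number of repeats grows with measuring activity and with elapsed time, and these are the dimensions of the main contrasts. Hypothesis 1 asks whether the gap between trained PHCUs with and without municipal action is wider at month 18 than at month 12. If part of the widening is the same people measured again, the result would be read as more sustained coverage when it partly reflects re-measurement. Hypothesis 3 applies a 10% relative criterion to the same quantity at month 6, and that criterion decides whether Arm 4 is replaced by Arm 3.

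**Working it through.** **1. The plan's own figure.** Inputs from the sample size section: 15,000 adults per PHCU, ICC 0.03, 12 PHCUs in Arm 1, 15 in each of Arms 2 and 3, and the three coverages above.
- Design effect: 1 + (15,000 − 1) × 0.03 = 450.97.
- Effective n: 12 × 15,000 / 450.97 = 399.1, and 15 × 15,000 / 450.97 = 498.9.
- A two-sided 5% z-test with unpooled variance gives 82.1% power for Arm 2 vs Arm 1 and 96.5% for Arm 3 vs Arm 2.

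The stated 82% and 96.5% reproduce. They treat the coverages as proportions of distinct adults.

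**2. Is repeat attendance certain?** 1500 × 12 = 18,000 and 1500 × 18 = 27,000 consultations, which is 1.2 and 1.8 per registered adult. Yes. Reading *new* consultations as first-time patients does not avoid this, since 18,000 already exceeds the 15,000 registered.

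**3. Is repeat measurement certain?** The planned coverages mean 15,000 × 0.0325 = 488, 15,000 × 0.075 = 1125 and 15,000 × 0.15 = 2250 measurements per PHCU by month 12. Divided by 18,000 these are 2.7%, 6.3% and 12.5% of consultations. At such rates repeat measurement is possible and plausible, but the figures do not force it.

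**4. Direction.** Let S be sheets per registered adult and r the share of sheets that are repeats. Distinct adults = S(1 − r). The sheet difference overstates the adult difference when S₂r₂ > S₁r₁. For Arm 2 vs Arm 1 this fails only if Arm 1's repeat share exceeds Arm 2's by a factor above 0.075/0.0325 = 2.3; for Arm 3 vs Arm 2 the factor is 0.15/0.075 = 2. With equal r the ratio of coverages is unchanged.

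**5. Illustrative size.** The documents give no repeat rate. Assumptions:
- The planned coverages are read as sheets per registered adult, c.
- Measuring takes no account of earlier measurement.
- Month-18 counts are 1.5 times the month-12 counts (not in the protocol).

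Distinct adults per registered adult are 1 − exp(−c) if visits are spread evenly, and 1 − (1 + c/k)^(−k) with k = 0.5 (assumed) if they concentrate in frequent attenders.

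| Time, arm | c | Even | k = 0.5 |
|---|---|---|---|
| Month 12, Arm 1 | 0.0325 | 0.0320 | 0.0310 |
| Month 12, Arm 2 | 0.075 | 0.0723 | 0.0675 |
| Month 12, Arm 3 | 0.15 | 0.1393 | 0.1229 |
| Month 18, Arm 2 | 0.1125 | 0.106 | 0.096 |
| Month 18, Arm 3 | 0.225 | 0.201 | 0.170 |

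- Arm 3 − Arm 2, month 12: 0.075 against 0.0670 and 0.0554, overstated by 12% and 35%.
- Arm 3 − Arm 2, month 18: 0.1125 against 0.0951 and 0.0731, overstated by 18% and 54%.
- Arm 2 − Arm 1, month 12: 0.0425 against 0.0403 and 0.0365, overstated by about 6% and 16%.

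**6. Hypothesis 1.** From month 12 to 18 the gap in sheets grows by 0.1125 − 0.075 = 0.0375. The gap in adults grows by 0.0951 − 0.0670 = 0.028 (even) or 0.0731 − 0.0554 = 0.018 (k = 0.5).

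**7. Hypothesis 3.** If Arms 3 and 4 reach the same number of adults but one has 0% repeats and the other 10%, the sheet counts differ by 1/(1 − 0.10) = 1.11. That is an 11% relative difference, above the 10% criterion.

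**The case against.** Several stronger readings are tempting, and the document does not support them.

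- *Providers measure at every consultation.* The request covers all adults who consult, which also fits one measurement per adult. Sheet use is discretionary, and planned measurement is 2.7–12.5% of consultations.
- *Repeat measurements must occur.* The consultation volumes prove repeat attendance only.
- *The arm difference is inflated.* This is likely, not certain. It depends on repeat shares that nobody has measured, and providers who skip patients already asked would shrink it. The planned contrasts are two-fold or more, and an equal repeat share leaves those ratios intact.
- *The proportion could exceed 1.* This is possible arithmetically but remote, given a highest planned value of 0.15.
- *The power calculation is wrong.* It reproduces.

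The strongest defence is that the tally sheet, care pathways and data management plan are in supplements not shown here. An already-measured item or a once-per-patient instruction may be there. Anonymity is also a deliberate choice, following an earlier project's validated method. Both points are fair. If the sheet has such an item, the sponsor can close this point by saying so in the outcome definition.

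The mismatch remains as the article describes the data: a numerator of sheets over a denominator of people, with no stated means of reconciling them.

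**Conclusion.** The concern holds in limited form. As described, the primary outcome is labelled a proportion of adults but is computed from measurements that cannot be de-duplicated. Coverage is overstated to whatever extent adults are measured more than once, and the absolute arm difference probably is too, increasingly so by month 18. Hypothesis 1 is the most exposed.

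The size cannot be fixed from the document. Overstatement of the Arm 3 − Arm 2 difference by 12–35% at month 12 and 18–54% at month 18 is illustrative only. It rests on measuring that ignores earlier measurement, an assumed visit distribution and, for month 18, an assumed 1.5-fold scaling. The corresponding month-12 range for Arm 2 − Arm 1 is about 6–16%. The point still deserves action because it concerns the primary outcome and later analysis cannot recover the missing information.

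**What to change.** **Preferred.** Add one tick box to the tally sheet: *AUDIT-C already completed for this patient during the study: yes / no*. Count only first measurements in the primary numerator. The sheets stay anonymous. The cost is one item and some recall error by patient or provider.

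**If sheets are already in use.** Redefine the outcome as *AUDIT-C measurements per 1000 registered adults* wherever coverage is used: the main outcome and hypotheses in the Introduction, the month-6 rule in Methods and analysis, the Primary outcome section, the tests of all three hypotheses, and the sample size section. State that it is not the proportion of adults reached. Add a sensitivity analysis over a range of repeat shares, allowed to differ by arm and between months 12 and 18. The cost is wording and one extra analysis.

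**Supporting evidence.** An *asked before?* item in the self-completed patient questionnaire would help set that range, but only roughly. At most 540 forms per round over 54 PHCUs is 10 per PHCU, or 120–150 per arm. At a repeat share of 15% the 95% margin is 1.96 × √(0.15 × 0.85 / 150) ≈ 0.06, about ±6 points before clustering. The forms come only from patients able to read and write, at months 3 and 13, so month 18 is not covered.
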